	**Working Alliance Inventory-Short form—therapist [41]**					
		Therapeutic alliance				Sessions 5, 11, and 23
	**Questionnaire on therapists’ perspective**					
		Perspective and satisfaction of the therapist regarding RC2S				Session 24

^a^RC2S: Remédiation Cognitive de la Cognition Sociale dans la Schizophrénie.

In addition to measures administered with both categories of participants, objective indicators of feasibility will be collected, including the safety of the study (comprising whether there are any adverse events reported), the number of participants who have completed therapy (at least 50% of the treatment completed), reasons for dropping out, duration of sessions, and the number of missed sessions and reasons.

### Intervention: RC2S

RC2S is an individualized computerized CR composed of 24 biweekly individual sessions of 1 hour with a therapist. The intervention is divided into 3 parts, as presented in Figure 1 and described in the subsequent section. RC2S provides a standardized approach regarding the material, duration, frequency, delivery of intervention, and CR principles and strategies, while also offering a personalized approach as a function of the person’s profile.

**Figure 1 figure1:**
[figure not shown]
Description of RC2S (Remédiation Cognitive de la Cognition Sociale dans la Schizophrénie) sessions.

During the first 2 sessions of therapy, a case formulation is elaborated to identify the strengths, weaknesses, and CR goals. Psychoeducation about social cognition and the impact of social cognitive impairments on functioning is presented. To complement the objective assessment of social cognition performed at baseline, the functional impacts of social cognitive impairments are assessed with the Échelle de répercussions fonctionnelles des troubles de la Cognition Sociale (ERF-CS; *Scale for the assessment of functional impacts of social cognitive deficits*) [38]. This semistructured interview explores the presence and impact of various social cognitive impairments in daily life. The interview also assesses how much the participant is bothered by these impairments. The results from the ERF-CS provide a detailed perspective on how social cognitive impairments disrupt the participant’s life. Furthermore, given the psychometric limitations of most available social cognitive tasks, particularly regarding the ecological aspect of these tasks, the ERF-CS provides in-depth and concrete information to build a case formulation and support the client while creating treatment objectives. In this project, treatment objectives will be developed with the Goal Attainment Scale (GAS) [28], a flexible scale that allows the elaboration of personalized objectives before starting treatment, with a reassessment at the end of therapy. The GAS is rated on a scale from −2 to +2. A score of 0 indicates that the participant has reached their initial goal. Scores of +1 or +2 are obtained if the participant has exceeded or greatly exceeded their initial goal. Scores of −1 and −2 are obtained if the participant did not completely reach their objective. When the objectives are set, an operational definition is established for each level of rating.

Weeks 2 to 11 of RC2S are dedicated to CR. During the first session of each week, stimuli such as photography, videos, and role-plays are used to teach strategies for social cognitive impairments, first for basic (eg, emotion recognition) and then for complex (eg, theory of mind) social cognitive processes. The number of paper-and-pencil sessions dedicated to each social cognitive domain, the exercises used to work on these domains, and the intensity of difficulty used are tailored based on the participant’s objective and subjective social cognitive impairments, as well as the treatment objectives. Evidence-based strategies used in CR are applied in RC2S (eg, repeated practice, scaffolding, verbalization, errorless learning, and information reduction).

During the second session of each week, digital relational simulations are used. During each simulation, the participant assists a character named Tom in different social scenarios presenting various types of relationships and interactions (eg, Tom is having an altercation with his boss or Tom initiates a conversation with an acquaintance). Depending on each participant’s individual difficulties, the order of presentation of the different scenarios is adapted to respect an increase in difficulty each week. For each scenario, the participant must read a short vignette introducing the simulation and answer the different questions on the *wheel of questions* (Figure 2A). The participant gathers information through the wheel of questions, including who will be involved in the simulation, where and when it is happening, what will be happening in the situation, why, and how. This initial analysis allows the participant to differentiate between what is a known fact in the situation and what is unknown, thus supporting the interpretations and choices that they will make during the simulation. Once the wheel has been completed, the participant begins the digital relational simulation. Each scenario is based on an algorithm of various propositions of behavioral patterns, and the scenario evolves based on the answer of the participant at each interaction. To assist Tom in navigating the different social scenes, the participant can choose among 3 types of behavior (ie, passive, aggressive, or assertive) based on social skills training and self-affirmation programs [24] (refer to Figure 2B for an example). The simulations are multimodal and integrative sessions that allow working on several social cognitive domains simultaneously including analyzing social context (social perception), emotions through verbal and nonverbal cues (emotion recognition), and understanding the mental states of Tom and his interlocutor (theory of mind) as well as their reactions (attributional style). For each interaction, the participant is encouraged to use the strategies learned during the paper-and-pencil sessions to perceive and interpret the different social cues and to verbalize these strategies. After the simulation, the participants’ choices are decomposed to focus on specific social cues. It is also possible to run the simulation again to experience another behavioral approach to the scene; this allows the participant to experience how different social approaches can lead to different outcomes for both Tom and his interlocutor.

**Figure 2 figure2:**
[figure not shown]
Digital relational simulations in RC2S (Remédiation Cognitive de la Cognition Sociale dans la Schizophrénie): (A) The wheel of questions presented before each simulation; (B) An example of a digital relational simulation with an avatar.

In addition to the 2 therapy sessions, each week, the participant is also assigned a home activity related to the objectives of CR to practice strategies learned in sessions and to support bridging in everyday life.

Week 12 (sessions 23 and 24) is dedicated not only to the transfer of acquired skills to daily life via role-play or activities in the community but also to a final assessment of the progress that was made. These last 2 sessions are thus also dedicated to assessing the current situation of the participants regarding their perception of the functional impacts of social cognitive impairments and their objectives. During these sessions, the ERF-CS will be administered again to assess the progression regarding the functional impacts of social cognitive impairments from the beginning of the therapy. Furthermore, goal attainment will be assessed again with the GAS to determine if the participant reached their goals partially or completely. This will also allow a discussion on how the participant can continue working on goals that are partially reached and set new goals to work on in the future.

### Statistical Analysis

#### Power

On the basis of previous psychosocial intervention studies with a similar population at our recruitment site, we expect an attrition rate of 20% for the participants with SSD [44,45]. Thus, for a targeted sample of 20 participants, the inclusion of a maximum of 4 additional participants should be expected, leading to 24 participants with SSD. This sample size will allow us to determine potential barriers for remote RC2S, improve the protocol and the adapted versions, determine the preliminary effects of the treatment, and obtain sufficient data to compute effect sizes for statistical power analyses in a future efficacy study. Although no stratification for gender and language will be applied, we aim, as much as possible, to recruit 10 English speakers and 10 French speakers, and we aim to have a proportion of men and women that is consistent with what is observed clinically.

As for the therapists, we aim to recruit 5 participants to obtain a variety of perspectives.

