**Results:**

So far, 45% (9/20) of participants with SSD (mean age 37.9, SD 9.3 years) have completed the project. They received a mean of 20.5 out of 24 (SD 3.5) sessions of RC2S. A total of 5 therapists also completed the project.

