#### Participants With SSD

We aim at recruiting 20 participants with SSD. For these participants, the inclusion criteria will be as follows: (1) a diagnosis of schizophrenia or a related psychotic disorder according to the Diagnostic and Statistical Manual of Mental Disorders, Fifth Edition; (2) being followed and treated by a clinician at the Douglas Mental Health University Hospital; (3) being aged ≥18 years; (4) having either a self-report or an objective impairment (≤1 SD) in at least 1 social cognition domain (ie, emotion recognition, theory of mind, attributional bias, or social perception); (5) being considered symptomatically stable and capable of using the web-based platforms, as judged by their primary clinicians (ie, psychiatrist, case manager, or psychologist); (6) having access to the internet and to a private space (a room where the participant can be alone); and (7) being able to nominate an emergency contact as the study is conducted remotely. For this group, the exclusion criteria will be as follows: (1) evidence of an organic cause for cognitive difficulties (eg, neurological disease and history of brain trauma), (2) history of intellectual disability or autism spectrum disorder, (3) being hospitalized at the time of recruitment, and (4) inability to speak or read French or English.

Participants with SSD will be recruited through convenience sampling at the Douglas Mental Health University Institute. Participants will be recruited from (1) direct reference of the treating psychologist at the Centre d’Intervention Psychologique Personnalisé pour la Psychose (Ci3P; a clinic dedicated to psychological treatments for psychotic disorders), (2) directly from the individual’s case manager following a clinic visit by the research coordinator to explain the research project, or (3) from our list of participants who were recruited in previous studies and gave their consent to be recontacted for future studies. A research assistant will call the participant to explain the research project, including the inclusion criteria, the assessment and treatment procedures, and the consent form. During this first contact, the research assistant will also assess access to the digital technology required for this project (eg, a smartphone, a tablet, or a computer).

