#### Data Analysis

To assess the acceptability, feasibility, safety, and implementation of remote North American English and French-Canadian versions of RC2S, descriptive statistics will be used to summarize the objective indicators and the quantitative answers from the questionnaires (eg, number of missed sessions). Open-ended questions in the RC2S+ Acceptability, Usability, Safety, Impact, and Satisfaction Questionnaire and the Questionnaire on therapists’ perspective will be classified into categories associated with the implementation of remote psychosocial interventions [46,47]. These analyses will notably determine if the participants with SSD and the therapists perceive the remote administration of the culturally adapted versions of RC2S as feasible and acceptable. We will assess the engagement of participants (eg, motivation, number of sessions completed, and number of completers), the perception of the usefulness of the intervention by both participants with SSD and therapists, and the overall satisfaction with the intervention and the delivery mode. This information is necessary to determine if the remote administration of the culturally adapted versions of RC2S is feasible and acceptable before planning an efficacy trial. These results will also provide information to determine if some modifications to the protocol are necessary.

For the objective regarding the preliminary effect of RC2S on primary and secondary outcomes, we will use an intention-to-treat approach, including the data of all participants who entered the study. Effect sizes will be calculated by subtracting scores at baseline from posttest scores and dividing them by the SD of baseline scores for both primary and secondary outcomes. Linear mixed models for repeated measures will be used to assess the effect of RC2S on both primary and secondary outcomes, with fixed effects of time. Gender, language, and the severity of social cognitive impairments will be used as covariates. Although *P* values will be calculated, we will be mostly interested in the effect sizes to guide power analyses for a future efficacy trial.

For other outcomes, including the in-session questionnaires, descriptive statistics will be used to summarize the data for both groups of participants. Motivation toward treatment and perception of therapeutic alliance will be correlated with primary and secondary outcomes, as well as with the objective indicators of feasibility and acceptability.

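### Minor arithmetic slip: the attrition allowance is 20% of the target, not of those enrolled, so if 20 is the number to be retained, 24 enrolled gives about 19

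*Protocol article*

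**What the plan says.** The Power section of the protocol article gives three linked figures.

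- **Rate:** "we expect an attrition rate of 20% for the participants with SSD", based on earlier psychosocial studies at the same site.
- **Target:** the allowance is worked out "for a targeted sample of 20 participants".
- **Result:** "the inclusion of a maximum of 4 additional participants should be expected, leading to 24 participants with SSD".

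The result is presented as following from the rate. No formula is shown, and no significance level, power or effect size enters the derivation. One stated purpose of the sample is to "obtain sufficient data to compute effect sizes for statistical power analyses in a future efficacy study".

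Elsewhere the number 20 has more than one role. Under Recruitment, Participants With SSD, it is a recruitment aim: "We aim at recruiting 20 participants with SSD". The abstract's Methods uses it as the number included to receive the intervention. The abstract's Results uses it as the denominator for completers: "45% (9/20) of participants with SSD (mean age 37.9, SD 9.3 years) have completed the project". For the preliminary-effect analysis, the Data Analysis section states: "we will use an intention-to-treat approach, including the data of all participants who entered the study".

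**The concern.** An attrition rate is a proportion of the people who enter. To retain a given number, one divides that number by the retained fraction. The plan instead adds 20% of the target to the target, which always falls short of what the stated rate requires. The three printed figures (20%, 20 and 24) therefore do not agree if 20 is to be the number left after attrition.

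The number retained matters to the plan's own purpose. Effect sizes are computed from posttest minus baseline scores, so a participant with no posttest contributes no observed change. Goal attainment, a primary outcome, is re-rated at session 24. A reader planning the later efficacy trial would expect 20 such observations, while the plan's own assumption gives slightly fewer.

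The wording adds to this. The 20% is an expected rate, so actual losses may be higher or lower, yet the 4 extra participants are described as a maximum.

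**Working it through.** **Inputs** (all from the Power section): target n = 20; attrition d = 0.20; stated total N = 24.

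**1. Reproduce the plan's figure.** n × (1 + d) = 20 × 1.20 = 24, which matches exactly. The 4 added is 0.20 × 20, that is, 20% of the target.

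**2. Allowance that matches the stated rate.** n / (1 − d) = 20 / 0.80 = 25. Check: 25 × 0.80 = 20.0.

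**3. What 24 delivers.** 24 × 0.80 = 19.2 expected to be retained, a shortfall of 20 − 19.2 = 0.8.

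**4. Attrition that 24 can absorb.** (24 − 20) / 24 = 4/24 = 16.7%, against the stated 20%.

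**5. Replacement reading.** Suppose 20 enter, 4 leave and 4 are added in their place. The replacements face the same 20%, so 0.8 of a further person is needed, then 0.16, and so on: 20 + 4 + 0.8 + 0.16 + … = 20 / (1 − 0.20) = 25. This reading also leads to 25.

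**6. Effect on precision.** With standard errors proportional to 1/√n, √(20/19.2) = 1.02, an increase of about 2%.

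**7. Chance of reaching 20.** This assumes that each participant independently has an 80% chance of being retained, which is my assumption and not the plan's.

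| Enrolled | Expected retained | P(at least 20) | P(at least 19) |
|---|---|---|---|
| 24 | 19.2 | 0.46 | 0.66 |
| 25 | 20.0 | 0.62 | 0.78 |

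Even with 25 enrolled there is a 38% chance (1 − 0.62) of ending below 20. These probabilities show that 20% is an expectation with spread around it. They do not show that one enrollee decides whether the study succeeds.

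**The case against.** The strongest reply is that the matter is too small to count. The difference is one enrollee, well within the uncertainty of a rate borrowed from earlier studies. Nothing in the article depends on having exactly 20: there is no power statement and no decision threshold, and the Limitations section says the study does not aim to establish efficacy. The preliminary-effect analysis takes in everyone who entered, and the feasibility indicators use dropouts as well. All of this stands, and it limits the point to a correction of figures. It does not make the figures agree.

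A second reply is that the Power section never says 20 means completers, and the recruitment section treats 20 as the number recruited. This also stands in part. However, an attrition allowance on top of a target has little purpose unless the target is what should remain, and the abstract counts completers against 20. The ambiguity is itself a reason to restate the number. The replacement reading does not rescue 24, as step 5 shows.

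A reader might also infer that enrolment closes at 24, so that any shortfall cannot be made up. The article does not say so. The sentence can be read as a recruitment forecast, and nothing in the text bars replacing a further dropout. The same holds for inferring that the study is underpowered, because no power was claimed.

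**Conclusion.** The point holds as a minor arithmetic correction. The allowance is computed as 20 × 1.20 = 24, whereas the stated attrition rate requires 20/0.80 = 25. If 20 is the number to be retained, 24 enrolled gives about 19, and 24 is enough only at attrition of 16.7% or lower. The size is 0.8 of a completer and about 2% in the standard error.

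The conclusion rests on two conditions: that the 20% applies to everyone enrolled, and that 20 is a retention target. The abstract's count of completers supports the second, but the Power section does not state it. The documents do not support calling this a threat to the study's validity or to its planned analysis.

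**What to change.** - In the Power section, state that 20 is the number of completers sought. The Measures section counts therapy as completed at 50% or more of treatment, while the effect sizes need a posttest, so say which of the two is meant.
- Restate the total as either *24 enrolled, about 19 expected completers at 20% attrition* or *25 enrolled for 20 expected completers*.
- Replace the description of 4 as a maximum with wording that treats the loss as an expectation.
- Align the abstract's Methods and the recruitment section, so that the number enrolled and the number to be retained are told apart wherever 20 appears.

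The cost is a wording change that makes the printed figure slightly less favourable (about 19 rather than 20), or one additional participant. No analysis changes.

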#### Data Analysis

To assess the acceptability, feasibility, safety, and implementation of remote North American English and French-Canadian versions of RC2S, descriptive statistics will be used to summarize the objective indicators and the quantitative answers from the questionnaires (eg, number of missed sessions). Open-ended questions in the RC2S+ Acceptability, Usability, Safety, Impact, and Satisfaction Questionnaire and the Questionnaire on therapists’ perspective will be classified into categories associated with the implementation of remote psychosocial interventions [46,47]. These analyses will notably determine if the participants with SSD and the therapists perceive the remote administration of the culturally adapted versions of RC2S as feasible and acceptable. We will assess the engagement of participants (eg, motivation, number of sessions completed, and number of completers), the perception of the usefulness of the intervention by both participants with SSD and therapists, and the overall satisfaction with the intervention and the delivery mode. This information is necessary to determine if the remote administration of the culturally adapted versions of RC2S is feasible and acceptable before planning an efficacy trial. These results will also provide information to determine if some modifications to the protocol are necessary.

For the objective regarding the preliminary effect of RC2S on primary and secondary outcomes, we will use an intention-to-treat approach, including the data of all participants who entered the study. Effect sizes will be calculated by subtracting scores at baseline from posttest scores and dividing them by the SD of baseline scores for both primary and secondary outcomes. Linear mixed models for repeated measures will be used to assess the effect of RC2S on both primary and secondary outcomes, with fixed effects of time. Gender, language, and the severity of social cognitive impairments will be used as covariates. Although *P* values will be calculated, we will be mostly interested in the effect sizes to guide power analyses for a future efficacy trial.

For other outcomes, including the in-session questionnaires, descriptive statistics will be used to summarize the data for both groups of participants. Motivation toward treatment and perception of therapeutic alliance will be correlated with primary and secondary outcomes, as well as with the objective indicators of feasibility and acceptability.

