### Measures

For participants with SSD, the primary outcomes will consist of (1) therapy goal attainment (ie, assessing if the participants have not reached, reached partially, or reached completely their initial CR goals in daily life) and (2) the 4 main domains of social cognition (emotion recognition, social knowledge, theory of mind, and attributional bias) in addition to the functional impact of social cognitive impairments. The secondary outcomes will include measures of symptoms (positive and negative symptoms, depression, and social anxiety), functioning, recovery, and cognitive biases. In addition, complementary outcomes pertaining to different aspects of RC2S (eg, program interface, cultural adaptation, and ease of use) and remote delivery will be assessed through in-session questionnaires. These will include motivation toward the treatment, perception of therapeutic alliance, suicide risk, engagement toward treatment, feeling of immersion in the digital relational simulations, and aspects related to implementation (eg, attitudes toward the intervention such as its usefulness, the probability of using it, and the perception about one’s ability to use the intervention).

For therapists, in-session questionnaires will be administered to assess their perception of their client’s motivation toward treatment, therapeutic alliance, and their perspective and satisfaction toward RC2S. The details regarding the different measures and time of administration for both categories of participants are presented in Table 1.

**Table 1 table1:** List of measures included in the study.

Name of the measure and domain assessed					Time point	

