**Participants receiving RC2S^a^**						
	**Primary outcomes**					
		**Goal Attainment Scale [28]**				
			Therapy goals attainment	Sessions 1 and 24		

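### The baseline SD is an unsuitable standardiser for the Goal Attainment Scale, so its planned effect size is likely inflated and cannot guide a future power analysis

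*Protocol article*

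**What the plan says.** The Data Analysis section gives a single rule: "Effect sizes will be calculated by subtracting scores at baseline from posttest scores and dividing them by the SD of baseline scores". It makes no exception for any outcome; the scope is "dividing them by the SD of baseline scores for both primary and secondary outcomes". The same section says that effect sizes, more than P values, are of interest because they will inform power calculations for a later efficacy trial. The Power section and the Discussion overview repeat that purpose.

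The Measures section makes goal attainment a primary outcome: "the primary outcomes will consist of (1) therapy goal attainment". Table 1 times the GAS at "Sessions 1 and 24".

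The Intervention: RC2S section describes the scale. It "allows the elaboration of personalized objectives before starting treatment, with a reassessment at the end of therapy". On scoring, "The GAS is rated on a scale from −2 to +2", and "A score of 0 indicates that the participant has reached their initial goal". Positive scores mean the goal was exceeded; −1 and −2 mean it was not fully reached. The text on week 12 says that goal attainment is assessed a second time in the closing sessions.

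**The concern.** Dividing by the baseline SD makes sense when baseline scores vary freely between people, because the SD then expresses a change in units of natural variability. The GAS does not work that way. Each score is relative to the person's own goal, and the goal is written when the first rating is made. A goal not yet reached leaves only two possible values out of five. The spread at session 1 then depends on how ambitiously each goal was scaled.

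At stake is the use of the number. A GAS effect size built on a compressed denominator would appear beside those of the social cognition tests as if comparable, and could be carried into the sample size of the planned randomised trial.

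**Working it through.** **Plan's own figures.** The article states no GAS baseline SD and no GAS effect size, so there is none to reproduce. Its sample-size figure reproduces as 20 × 1.2 = 24; it does not bear on this point.

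**Inputs from the protocol article.** Target sample 20 (Participants With SSD); GAS range and meaning of the levels (Intervention: RC2S); effect-size formula (Data Analysis).

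**Assumptions made here.** Nobody sets a goal already met at session 1. There is one GAS score per person. The starting split and the final mean are not in the article, so a range is shown.

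**Formulas.** With k of n participants starting at −1 and the rest at −2:
- baseline mean = −2 + k/n
- baseline SD = √[k(n − k) / (n(n − 1))]
- d = mean gain / baseline SD

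Example, k = 2 and n = 20: mean = −1.90; SD = √(36/380) = 0.308; a final mean of 0 gives d = 1.90/0.308 = 6.2.

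| k of 20 at −1 | Baseline mean | Baseline SD | d, half-level gain | d, one-level gain | d, final mean 0 |
|---|---|---|---|---|---|
| 0 | −2.00 | 0 | undefined | undefined | undefined |
| 1 | −1.95 | 0.224 | 2.24 | 4.47 | 8.7 |
| 2 | −1.90 | 0.308 | 1.62 | 3.25 | 6.2 |
| 4 | −1.80 | 0.410 | 1.22 | 2.44 | 4.4 |
| 5 | −1.75 | 0.444 | 1.13 | 2.25 | 3.9 |
| 10 | −1.50 | 0.513 | 0.97 | 1.95 | 2.9 |
| 13 | −1.35 | 0.489 | 1.02 | 2.04 | 2.76 |

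**Bounds.** The SD is largest at the even split, 0.513 (0.511 for n = 24). For a fixed gain, d is therefore smallest there: 1/0.513 = 1.95 for one level and 0.5/0.513 = 0.97 for half a level. For a final mean of 0, the smallest d over all splits is 2.76, at k = 13. With the SD computed without the n − 1 correction, the minimum is 2.83. Both round to 2.8.

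**Several goals per person.** Averaging goals cannot raise the maximum SD, since the average still lies between −2 and −1. With three independently rated goals and an even chance of each level, the SD falls to about 0.5/√3 = 0.29.

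**Effect on a future sample size.** Assume a two-arm comparison with two-sided 5% alpha and 80% power. By the normal approximation, n per arm = 2(1.960 + 0.842)²/d² = 15.7/d². For d = 2.92, the even split with a final mean of 0, this is 1.84, or 2 per arm. For an illustrative d = 0.5 it is 62.8, or 63 per arm.

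**Alternative reading.** If session 1 only sets the goals and yields no score, there is no baseline value and no baseline SD, and the formula cannot be computed for the GAS. Table 1 and the week 12 text suggest that a session 1 rating exists, but neither reading makes the rule work.

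**The case against.** The strongest defence is that the preliminary effect is an exploratory objective. The Limitations section disclaims any aim to establish efficacy, and feasibility, acceptability, safety and implementation do not use this formula. The four social cognition tests are not scored against a personal goal, so their effect sizes are untouched. All of this stands and limits the reach of the point. It does not remove it, because the article names effect sizes as the main product of this analysis and gives them a use.

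Several stronger readings are tempting, but the article does not support them:

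- A reader might infer that the GAS has almost no baseline variance, so that d must be undefined or absurd. Nothing in the article gives everyone the same starting level. Two unmet levels exist, and a mixture gives a finite d, as low as 0.97 for a half-level gain.
- A reader might infer that d hardly depends on the intervention. At a fixed split, d is proportional to the mean gain: at the even split, gains of 0.5, 1 and 1.5 levels give 0.97, 1.95 and 2.92.
- A reader might infer that a pre-post time effect on the GAS tests nothing because everyone moves up. A participant may make no progress, and one who starts at −1 may fall to −2. The fair reservations are the floor at −2 and the missing control group, which the article acknowledges.
- A reader might see a contradiction between the five-level scale and the Measures wording, "assessing if the participants have not reached, reached partially, or reached completely their initial CR goals in daily life". That wording is a gloss in a list of outcomes; the scoring rule is the five-level one, and no stated analysis uses three levels.

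**Conclusion.** The point holds in a limited form. For the GAS, and among the primary outcomes only for the GAS, the baseline SD is the wrong denominator. If no goal is already met when it is set, the SD lies between 0 and about 0.51 for 20 participants and reflects the assignment of starting levels. The resulting effect size is likely inflated and not comparable with those of the other outcomes. How large it would be depends on a starting split and a mean gain that the article does not give, so the table shows a range and predicts no single value. The same final mean of 0 yields anything from about 2.8 to 8.7, or no value at all, according to the starting split alone. That is enough to rule out a GAS d as an input to a power calculation.

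**What to change.** In the Data Analysis section, exclude the GAS from the baseline-SD effect size and state that no GAS d will be used for future power calculations. Report the session 24 GAS on the full −2 to +2 scale:

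- the mean of the participants' scores (averaged over goals where there are several) with a 95% CI against 0, stating how many participants were rated;
- the proportion at 0 or above with an exact CI. The denominator is all participants who entered, in line with the stated intention-to-treat approach, and those without a session 24 rating count as not attained. Add an observed-case sensitivity analysis. The rule is needed because the article expects 20% attrition.

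Unstandardised change in levels may be added as description if session 1 yields a score.

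The cost is one paragraph of analysis wording; no new data are needed, since the session 24 rating is already scheduled. The downside is that the GAS will have no standardised effect size alongside the other outcomes.
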